#### Statistical analysis methods

2.13.2

Clinical characteristics and safety outcomes will be summarized using descriptive statistics. Unless otherwise stated, continuous data will be statistically described using mean (± standard deviation) or median (minimum, maximum). Categorical data will be statistically described using frequencies (percentages). Cox proportional hazard models will be used for univariate and multivariate survival analyses, with HRs and 95% confidence intervals (CIs) calculated. Subgroup analyses will be conducted by the characteristics of patients and liver metastases (liver oligometastases or multiple liver metastases). Both the intention-to-treat (ITT) population and the per-protocol population will be used for efficacy and safety analyses. The worst-case imputation and complete-case analysis will be performed as sensitivity analyses to handle the missing data and dropouts (24). The SAS 9.2 (or higher) will be used for statistical analyses, using a one-sided 0.05 hypothesis test of superiority, and 95% CIs and *P* values will be reported for group comparisons.

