For AEs related to fruquintinib, the dose of fruquintinib will be reduced to 3 mg/day for Grade ≥3 toxicity, and further reduced to 2 mg/day if necessary (8, 23). After AEs resolve to Grade 0–1 or to baseline levels, drug administration as scheduled will be resumed. Close monitoring for proteinuria and hypertension will be performed per protocol throughout the study. Importantly, for proteinuria of grade 2 or higher (≥2g/24h), fruquintinib will be temporarily withheld until the level decreases to <1g/24h, after which treatment can be resumed at a reduced dose. Permanent discontinuation will be required in cases of nephrotic syndrome or if proteinuria does not recover to <1g/24h. Hypertension will be managed according to American Heart Association guideline. Grade 3 hypertension will necessitate treatment interruption; upon recovery to grade 1, therapy can be restarted at a lower dose. Any grade 4 hypertension will result in permanent treatment discontinuation. Dose adjustments of sintilimab are not permitted in this trial. To manage intolerable AEs, sintilimab administration will be withheld until toxicity recovers to Grade 0–1 or to baseline levels. The maximum permitted interruption of sintilimab due to corticosteroid use for managing immune-related adverse events will not exceed 12 weeks.

Investigators must ensure that patients receive the prescribed radiation dose as defined in the protocol. If a treatment-related adverse event (TRAE) necessitates an interruption of radiotherapy, the pause should not exceed two weeks. If an interruption extends beyond two weeks due to TRAE, the decision to resume radiotherapy must be made following careful evaluation by investigators. In such cases, the patient’s treatment plan will be considered a major protocol deviation, and the patient will be regarded as a dropout. If radiotherapy is interrupted due to TRAE, administration of the study drug should be suspended concurrently. To facilitate treatment completion, appropriate prophylactic measures and supportive nutritional care are recommended. Treatment may resume once the AE recovers to CTCAE Grade 2 or lower.

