#### Secondary outcomes

2.9.2

Objective response rate (ORR), defined as the proportion of subjects with a CR or PR by RECIST v1.1;Disease control rate (DCR), defined as the proportion of subjects with a CR, PR, or SD by RECIST v1.1;Overall survival (OS), defined as the time from treatment initiation to death from any cause;The incidence, severity, and association of any AEs with study drugs, treatment-emergent adverse events (TEAEs), SAEs, and immune-related adverse events (irAEs).

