### Discontinuation/withdrawal/loss to follow-up

2.12

In the event of participant withdrawal or study termination, investigators will continue to collect data on AEs and survival status. For subjects who withdraw but remain eligible for follow-up, all procedures outlined in **Supplementary Table 1** will be performed. Participants who discontinue the study for reasons other than disease progression must undergo an imaging assessment upon treatment completion. If a scheduled follow-up visit is missed, the investigator will make attempts to contact the participant to reschedule the appointment and will document the outcome of these efforts.

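### Safety is assigned to the per-protocol population as well as ITT; a toxicity-driven dropout rule that only the radiotherapy arm can trigger would bias the per-protocol adverse-event table

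*Protocol article*

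**What the plan says.** The protocol article deals with this in five places.

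- **Analysis populations (2.13.2).** "Both the intention-to-treat (ITT) population and the per-protocol population will be used for efficacy and safety analyses". The sentence ranks neither population first, and the article names no population based on treatment received.
- **Method for safety (2.13.2).** "Clinical characteristics and safety outcomes will be summarized using descriptive statistics".
- **Radiotherapy interruption (2.8).** "If an interruption extends beyond two weeks due to TRAE, the decision to resume radiotherapy must be made following careful evaluation by investigators". The next sentence says that in such cases the patient's "treatment plan will be considered a major protocol deviation, and the patient will be regarded as a dropout".
- **Safety as an endpoint (2.9.2).** The secondary outcomes include "The incidence, severity, and association of any AEs with study drugs", together with treatment-emergent, serious and immune-related events. Section 2.13.1 adds that the fruquintinib-only arm serves partly as a safety reference.
- **After withdrawal (2.12).** "investigators will continue to collect data on AEs and survival status".

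**The concern.** A per-protocol population is chosen by what happened after randomisation. For safety this is a problem whenever the reason for leaving the set is itself a safety event, and section 2.8 creates that situation: treatment-related toxicity that stops radiotherapy for long enough turns the patient into a major deviator.

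The rule is also one-sided. Section 2.5 gives radiotherapy to the intervention arm only, so neither the sintilimab plus fruquintinib arm nor the fruquintinib arm can lose a patient through it. It is the only event that the article labels a major deviation. Any resulting error would favour the new combination, both against its direct comparator and against the arm kept as a safety reference.

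Because safety is summarised descriptively, the choice of numerator and denominator is in effect the whole analysis. With 24 patients in the arm, removing one or two changes a percentage visibly.

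**Working it through.** **Plan's own figure.** The article states no AE rate, no expected number of radiotherapy interruptions and no size for either safety population, so there is nothing to reproduce. The only input taken from the article is the intervention arm size of 24 (2.13.1). The other counts below are assumptions.

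**Step 1: who can leave the per-protocol set.** Reading 2.5, 2.8 and 2.13.2 together:

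1. Only intervention patients receive radiotherapy (2.5).
2. A treatment-related AE that interrupts it for more than two weeks makes the patient a major deviator and a dropout (2.8).
3. Safety is analysed in the per-protocol set (2.13.2).
4. Major deviators are left out of that set. This is the usual meaning of the term; the article does not state it.

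From 1 to 4, the per-protocol AE table loses intervention patients because of toxicity and loses none from the other arms by this route.

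**Step 2: size.** Let k be the number of such dropouts, each counted as having a severe AE, and x the number of other intervention patients with a severe AE.

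- All patients: (x + k)/24
- Per-protocol: x/(24 − k)
- Shortfall: (x + k)/24 − x/(24 − k) = (k/24) × [1 − x/(24 − k)]

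With x = 8:

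| k | All patients | Per-protocol | Shortfall (points) |
|---|---|---|---|
| 0 | 8/24 = 33.3% | 8/24 = 33.3% | 0 |
| 1 | 9/24 = 37.5% | 8/23 = 34.8% | 2.7 |
| 2 | 10/24 = 41.7% | 8/22 = 36.4% | 5.3 |
| 3 | 11/24 = 45.8% | 8/21 = 38.1% | 7.7 |
| 4 | 12/24 = 50.0% | 8/20 = 40.0% | 10.0 |

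The shortfall is smallest when the AE is common and largest when it is rare. With x = 12 and k = 1 it is 54.2% − 52.2% = 2.0 points. With x = 5 and k = 4 it is 37.5% − 25.0% = 12.5 points. These are the extremes over x = 5 to 12 and k = 1 to 4.

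**Step 3: the ITT table.** It keeps all 24 patients, so the shortfall above does not arise. Its own weakness is dilution by patients who never start treatment. If one of 24 never starts and 8 have a severe AE, ITT gives 8/24 = 33.3% and treated patients give 8/23 = 34.8%, a difference of 1.5 points.

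**The case against.** **The plan also has an ITT safety table.** This is the strongest reply, and it stands. ITT retains the toxicity dropouts, section 2.12 continues AE collection after withdrawal, and a reader with both tables could see the gap. A reader might infer that the combination's AE rates will be understated throughout. The documents do not support that; only the per-protocol table is exposed. The reply does not rescue that table, though. The article gives it equal standing, and it would discard events that the trial has collected.

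**The per-protocol set is not defined here.** This is true, and a full protocol or analysis plan may define it. Exclusion is therefore an inference. It is a reasonable one, because the article applies both the major-deviation and the dropout label.

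**The trigger is length of interruption, not grade.** This also stands. A reader might infer that the patients with the worst radiotherapy toxicity are removed. The rule does not say so: the AE must be treatment-related but need not come from radiotherapy, and severe toxicity without a pause of more than two weeks stays in. So does toxicity that appears after the last of the 5, 10 or 13 SBRT fractions and any low-dose fractions. Section 2.8 ties resumption to recovery to Grade 2 or lower, which suggests that long pauses mainly reflect higher-grade events, but this is indirect.

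**The size can be made to look dramatic.** If only 4 of 24 patients had severe radiotherapy toxicity (16.7%) and 3 of them were dropped, the per-protocol rate would be 1/21 = 4.8%, a 3.5-fold understatement. The arithmetic is right, but those counts are one extreme choice with no basis in the documents.

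**Worst-case imputation is planned for dropouts.** In 2.13.2 it is a sensitivity analysis for missing data and dropouts. It does not correct a table from which patients with recorded AEs have been removed.

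**Conclusion.** The concern holds in a limited form. Assigning safety to the per-protocol population is a stated choice. Combined with the interruption rule in 2.8, it would understate AE rates in the intervention arm of the per-protocol table only. In the illustration the shortfall is 2.0 to 12.5 percentage points for one to four such dropouts among 24 patients, and zero if there are none.

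This rests on three assumptions: major deviators leave the per-protocol set, each such dropout counts as a severe AE, and the counts are as chosen. The direction follows from the first assumption together with the dropouts' having the event being tabulated, which for treatment-related AEs is true by definition of the rule. The size depends on the other two.

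The change should be made, but the trial does not stand or fall on it. Safety is a secondary, descriptive endpoint, the ITT table limits the damage, and the primary PFS comparison is untouched.

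**What to change.** In 2.13.2, replace the shared sentence on populations with two statements:

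- Safety is summarised in all patients who received at least one dose of sintilimab or fruquintinib or at least one radiotherapy fraction, grouped by treatment received.
- The per-protocol population is used for efficacy only.

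An ITT safety table may stay as a supplement. Patients classed as dropouts under 2.8 then remain in the main AE tables with their events, consistent with the continued collection in 2.12. The interruption rule itself need not change for this purpose.

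The cost is about one sentence. It needs no new data, no extra patients and no change to the primary analysis. It should be settled before any safety data are tabulated by arm.

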**Figure 2 f2:**
[figure not shown]
An example of target area delineation and radiation dose distribution for two patients. The top row **(A–C)** represents a patient with liver oligometastasis receiving 40 Gy/10 F irradiation, with the images displayed in axial, coronal, and sagittal planes. The bottom row **(D–F)** represents a patient with multiple liver metastases receiving 10 Gy/5 F irradiation, with the images displayed in axial, coronal, and sagittal planes.

Patients in the control group will be treated with sintilimab plus fruquintinib. A 21-day treatment cycle of sintilimab (200 mg) will be given intravenously on day 1 of each cycle, and a 21-day treatment cycle of fruquintinib (5 mg) will be given orally on days 1 through 14 of each cycle. Patients in the standardized treatment group will be treated with fruquintinib (5 mg) only, and a 21-day treatment cycle of fruquintinib will be given on days 1 through 14 of each cycle.

For all included patients, CT scans will be repeated every 12 weeks during the treatment to evaluate the efficacy, and the regimen will be continued if the response is evaluated as complete response (CR), partial response (PR), stable disease (SD), or non-progressive disease (PD). Sintilimab is administered for no more than 2 years. No dose adjustments of sintilimab are permitted throughout the study. Fruquintinib is continued until toxicity is intolerable, PD, or death.

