#### Tumor imaging at the end of treatment and during the follow-up

2.7.3

For subjects who complete treatment or discontinue treatment for reasons other than disease progression, the tumor imaging assessment should be performed. Subsequent imaging assessments should continue at the protocol-specified time points until one of the following occurs: initiation of a new anti-cancer therapy, objective disease progression, death, or study completion, whichever comes first.

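### The complete-case sensitivity analysis can exclude patients from the radiotherapy arm alone, because prolonged toxicity-related radiotherapy interruption is classed as dropout

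*Protocol article*

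**What the plan says.** All references are to the protocol article.

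- **Missing data (section 2.13.2).** "The worst-case imputation and complete-case analysis will be performed as sensitivity analyses to handle the missing data and dropouts". No endpoint is named and neither method is defined.
- **Populations and model (section 2.13.2).** "Both the intention-to-treat (ITT) population and the per-protocol population will be used for efficacy and safety analyses". For the time-to-event endpoints, "Cox proportional hazard models will be used for univariate and multivariate survival analyses".
- **Who is a dropout (section 2.8).** "If an interruption extends beyond two weeks due to TRAE, the decision to resume radiotherapy must be made following careful evaluation by investigators". Such a case counts as a major protocol deviation, "and the patient will be regarded as a dropout".
- **Who can meet that rule (section 2.5).** Liver radiotherapy belongs to the intervention group only. "Patients in the control group will be treated with sintilimab plus fruquintinib".
- **Follow-up after stopping.** Section 2.7.3, for patients who finish or stop treatment without progression: "Subsequent imaging assessments should continue at the protocol-specified time points until one of the following occurs" (new anti-cancer therapy, progression, death or study completion). Section 2.12, for withdrawal: "investigators will continue to collect data on AEs and survival status".

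**The concern.** PFS and OS are times to an event. A patient who leaves early still contributes the time observed so far, and a Cox model uses it through censoring. A complete-case analysis throws that time away. It also conditions on something that happened after randomisation, so the groups compared are no longer the randomised groups.

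Here the loss need not be balanced. The section 2.8 rule creates a class of dropout that the control arm cannot enter, and its trigger is toxicity. If section 2.13.2's dropouts include that class, complete-case analysis removes patients from the radiotherapy arm with no counterpart removed from control. What is at stake is how far this sensitivity analysis can be trusted as support for the primary comparison of intervention with control.

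**Working it through.** The plan gives no figure for this effect, so there is none to reproduce. The check has a textual part and a numerical part.

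**1. Do the rules connect?** Section 2.8 and section 2.13.2 use the same term, dropout, and nothing in the article separates the two uses. Sections 2.7.3 and 2.12 keep imaging, adverse-event and survival data coming after treatment stops or the patient withdraws. A section 2.8 dropout will therefore often have usable PFS and OS data, which a complete-case analysis could discard.

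**2. How many patients?** Section 2.13.1 plans 24 intervention and 23 control patients and a 5% dropout rate. Of 24 patients, 5% is 24 x 0.05 = 1.2, 10% is 2.4 and 20% is 4.8. The 5% is an overall planning allowance. The article gives no rate for section 2.8 dropouts, so 10-20% is an assumption. With the planned medians (1.8 and 3.7 months), 18 months of accrual and 12 of follow-up, administrative censoring is only about 0.1% (control) and 3% (intervention). The sensitivity analyses therefore turn almost wholly on dropouts.

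**3. Direction, by formula.** Suppose there is no treatment effect and that in both arms a share q of patients has g times the hazard of the rest. Remove that share from the intervention arm only. At time zero the hazard ratio is

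HR = 1 / (1 + q(g - 1)).

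- q = 0.05: g = 1.5 gives 1/1.025 = 0.976; g = 3 gives 1/1.10 = 0.909.
- q = 0.10: g = 1.5 gives 1/1.05 = 0.952; g = 3 gives 1/1.20 = 0.833.
- q = 0.20: g = 1.5 gives 1/1.10 = 0.909; g = 3 gives 1/1.40 = 0.714.
- g = 1 gives 1.00 for any q.
- g = 0.67 gives 1/0.967 = 1.034 at q = 0.10 and 1/0.934 = 1.071 at q = 0.20.

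When g exceeds 1, fast progressors leave the control risk set early and the ratio climbs towards 1, so the Cox estimate lies between the starting value and 1. When g is below 1, the ratio drifts further above 1.

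**4. Size, by simulation under no effect.** 24 against 23 patients, exponential PFS with median 1.8 months (for patients outside the share q), Cox test at one-sided 0.05, removal from the intervention arm only:

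| Removed | Hazard multiplier g | Complete-case HR | One-sided false-positive rate |
|---|---|---|---|
| 5% (planned dropout) | 1.5-3 | about 0.97-0.98 | 6-7% |
| 10-20% (assumed) | 1.5-3 | 0.86-0.97 | 7-12% |
| any | 1 | 1.00 | no shift |
| 10-20% | 0.67 | 1.05-1.10 | bias against the intervention |

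With all randomised patients kept, the HR is about 1.00 and the false-positive rate 5-6%.

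**5. With a true effect.** This run has 200,000 patients per arm, a uniform control arm, HR 0.5 in intervention patients who do not drop out, and dropouts with g times the hazard of the rest of their arm. At q = 5/10/20% and g = 1.5-2, the HR with everyone kept is 0.51 / 0.52-0.53 / 0.54-0.57, against 0.50 in complete cases. At g = 1 both are 0.50. At g = 0.67, keeping everyone gives 0.49 / 0.48 / 0.46, so complete-case analysis disfavours the intervention.

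**6. Worst-case imputation.** Counting the same dropouts as events by one month gives HR 0.53 / 0.56 / 0.63 in the setting of step 5. Under no effect with g = 1.5-3 it gives 1.00-1.10, with a false-positive rate of 3-5%. It works against the intervention.

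**The case against.** The strongest reply is that little harm can follow. These are sensitivity analyses, while intention-to-treat and Cox analyses are retained. Section 2.13.2 does not tie the two methods to PFS, and both are ordinary for ORR and DCR. The definitions by endpoint may sit in a full protocol or SAP that is not shown. Follow-up continues after treatment stops, so a section 2.8 dropout may have complete PFS data and never leave a complete-case analysis. At the planned 5% dropout, about one patient of 24, the distortion is small.

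Most of this stands, and it limits the point. It does not remove it: the two printed rules share a term and can combine to exclude patients from one arm, and nothing in the article prevents that.

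A reader might infer three stronger things that the documents do not support.

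- **That the bias certainly favours radiotherapy.** This requires the excluded patients to progress faster than the others. It is plausible, because section 2.8 also suspends study drug when radiotherapy is interrupted for such an event, but no passage establishes it.
- **That worst-case imputation is invalid for PFS.** Counting a dropout as an event is a definable, conservative rule. Applied to section 2.8 dropouts it penalises the intervention arm only. What remains is that no event date, arm or endpoint is given, and that for ordinary dropouts in both arms a symmetric rule is not the worst case for a superiority claim.
- **That the two checks together would make a fragile result look robust.** When dropouts do worse, the two pull in opposite directions.

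**Conclusion.** The point holds in limited form. Complete-case analysis is unsuitable for PFS and OS, and the section 2.8 rule makes it open to exclusion in the intervention arm alone on a post-randomisation toxicity event. That is a defect whatever the sign of the resulting bias.

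Its size is small at the planned 5% dropout and becomes material only at the assumed 10-20% with dropouts who progress clearly faster; the ranges are in the table. They rest on exponential times, on assumed hazard multipliers, and on every section 2.8 dropout actually being removed. The primary intention-to-treat comparison is not affected, provided these patients stay in it with their follow-up.

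The per-protocol analysis may make the same exclusion, since a major protocol deviation would ordinarily leave that set. Agreement between the per-protocol and complete-case results would then not be independent corroboration.

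**What to change.** Change the statistical wording in section 2.13.2, with a cross-reference to section 2.8:

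1. Drop complete-case analysis for PFS and OS.
2. State that patients classed as dropouts under section 2.8 stay in the intention-to-treat PFS and OS analyses with all their follow-up. Censor only those truly lost, at the last adequate tumour assessment for PFS and the last date known alive for OS.
3. Keep worst-case imputation and define it. For PFS, count intervention-arm dropouts with missing follow-up as events at their last assessment and leave control-arm dropouts censored. For ORR and DCR, treat a missing response as non-response (for DCR, as no disease control).
4. Describe the per-protocol analysis as supportive only, and note that it may exclude patients from one arm.

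The change affects no patient's treatment, no visit and no sample size. Its cost is that the PFS sensitivity analysis becomes stricter on the intervention arm and may look less favourable.

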## Discussion

3

For mCRC patients, the primary goal of third-line therapy is to prolong disease control and maintain quality of life and performance status, and more than 50% of mCRC patients receive third-line therapy. However, approximately 90% of previously treated mCRC patients lack therapeutically available targets. Consequently, for mCRC patients, effective third-line and beyond therapies are relatively scarce.

Fruquintinib is a highly selective oral TKI. The FRESCO study demonstrated that for patients with mCRC who failed second-line therapy, the fruquintinib group had a significantly prolonged mOS compared with the placebo group (25). However, for third-line and beyond treatment of mCRC patients, targeted therapy alone does not provide satisfactory survival benefit to patients. Targeted therapy in combination with immunotherapy has been much explored in clinical studies and holds promising prospects. Importantly, about 70% of mCRC patients have liver metastases, and mCRC patients with liver metastases derive significantly less clinical benefit from immunotherapy compared to patients without (15, 26–28). In mice, liver metastasis can recruit immunosuppressive macrophages that promote antigen-specific T cell apoptosis in the liver. This can lead to systemic loss of T cells and can reduce the efficacy of immunotherapy (18).

In the era of cancer immunotherapy, the synergistic effect of radiotherapy and immunotherapy has been confirmed by several studies. Preclinical studies have shown that radiotherapy can clinically control hepatic tumors and stimulate anti-tumor immunity (29–31). In the liver metastasis model of CRC, liver-directed radiotherapy has the potential to remodel the hepatic immune microenvironment, effectively prevent the hepatic siphoning of T cells, and thereby restore the immunotherapeutic effect (32). Liver-directed radiotherapy significantly enhanced the proliferation and IFN-γ production of subcutaneous tumor dLN CD8^+^ and CD4^+^ T cells (18). This result was further enhanced in mice receiving combination therapy. Anti-PD-L1 did not increase the number of T cells in subcutaneous tumors in mice with liver metastases, and liver-directed radiotherapy alone did not modulate the number of T cells. However, the combination of the two significantly increased T cell infiltration into subcutaneous tumors (18). Therefore, we will utilize a time window of one week after the initiation of immunotherapy to implement liver-directed radiotherapy to inhibit the “phagocytosis” of activated T cells by liver metastatic lesions and the induction of apoptosis in these cells.

LDRT is often overlooked in clinical practice. This low-dose modality, despite having a relatively weak direct cytotoxic effect on tumor cells, can stimulate immunity by altering the tumor microenvironment and enhance the effect of immunotherapy. Specifically, LDRT can trigger the activation of tumor immunotherapy. It has the capacity to reprogram the tumor microenvironment from an immunosuppressed state to an immunostimulated one (33). Moreover, LDRT may eliminate the immune privilege characteristic of the liver, allowing immunotherapy to function more effectively. In Herrera et al.’s study, the proportion of CD8^+^ T cells at different radiation doses was observed, and 1 Gy was identified as the optimal low-irradiation dose (34). They also discovered that LDRT reversed tumor immune desertification and resistance to immunotherapy. It has been shown that the combination of high-dose and low-dose radiotherapy can modulate the immune microenvironment and significantly activate immunity, as well as enhance leukocyte infiltration in the tumor, without changing the total radiation dose (35).

However, these promising disease control and survival outcomes reported here are based on studies with small sample sizes, raising concerns about selection bias. It is necessary to conduct larger-scale prospective trials to further validate these findings. For safety considerations, patients with central nervous system metastases were excluded from this trial. However, given that about 3-5% of mCRC patients present with brain metastases, this exclusion criterion inevitably will limit the generalisability of the findings to the broader mCRC population. Similarly, patients without MSI-H will also limit the generalisability. Future studies may consider exploring the safety and efficacy of this regimen in this specific subgroup. Furthermore, the application of a one-sided superiority test will increase the risk of type I error.

In conclusion, this study is a randomized, controlled, multicenter phase II clinical study exploring the efficacy and safety of combining sintilimab with or without liver-directed radiation on the basis of fruquintinib in the third-line treatment for CRCLM. We expect that the combination of sintilimab and radiotherapy will improve disease control and prolong the survival time of patients compared to fruquintinib plus sintilimab alone. This study will be published in a peer-reviewed journal, providing strong evidence-based medical proof for third-line treatment of CRCLM.
